**Fig. 1 Fig1:**
[figure not shown]
Flowchart of the study: Randomization, sampling and monitoring of patients

#### Main outcome

According to the objectives of the study, the primary outcome will be a composite that considers the following variables:

Depressive symptom severity will be assessed via the Patient Health Questionnaire (PHQ-9) [40] using the Spanish validated version [41]: Percentage of patients with reduction ≥2 points. The PHQ-9 [40], validated Spanish version [41] is one of the questionnaires that assess the intensity of depression most widely used in pharmacological and psychological studies. It is a brief and self-applied scale whose objective is to help diagnose depression (DSM-IV criteria) and determine its severity. Similarly, it is also useful to monitor changes experienced by patients over time. It will be taken four times: at baseline, post-treatment, and at 3-month and 6-month follow-ups.

Control of diabetes will be measured by VR d = glycosylated haemoglobin (% ≤ 7 or % with a decrease of 0.50 baseline), HbA1c, fasting capillary blood glucose, weight (kg), height (cm), waist circumference (cm), and abdominal diameter (cm).

Pain intensity and physical limitation will be measured. Pain intensity will be assessed via the Faces Pain Scale – Revised (FPS-R) [42], a self-report measure in which the patient scores the chosen face with 0, 2, 4, 6, 8, or 10, counting from left to right, where 0 = no pain, and 10 = very much pain. Disability will be assessed via Roland-Morris Scale [43]: This scale is designed to reliably determine the level of physical disability resulting from non-specific low back pain. In this regard, ‘physical disability’ is defined as the limitation in the performance of daily activities between 0 (absence of disability for back pain) and 24 (maximum possible disability). A change in score only has clinical relevance if it is of 2 or more points, although the optimal threshold is between 3 and 4 [44–46]. VR d = % with decrease ≥2 points.

The composite would be weighted to give 1/3 or 1/2 to each of the main measures of depression, diabetes and pain, obtaining an aggregate score. The calculation of the weighting of the composite variables would be performed by means of multiple regression.

#### Secondary outcomes

##### Sociodemographic variables

The following sociodemographic data will be collected: gender, age, marital status (single, married/long-term relationship, separated/divorced, widowed), education (years of education), occupation and economical level.

##### Mini-International Neuropsychiatric interview (MINI)

This is a short structured diagnostic psychiatric interview that yields key DSM-IV and ICD-10 diagnoses [47]. The MINI can be administered in a short period of time and clinical interviewers only need brief training. The MINI has been translated into Spanish and the Spanish version validated [47]. This psychiatric interview will allow the diagnosis of depression to be made at baseline in the study.

##### SF-12 Health Survey

This is an instrument that measures the state of perceived health. It consists of 12 items that measure 8 dimensions. The calculation of the scores is based on reference standards, on a scale of 0 (worst possible health status) to 100 (best possible health status). The SF-12 has good psychometric qualities [48] and is validated in Spanish [49].

##### CSRI Spanish version [39, 50]

Questionnaire for collecting information about the use of health and social care services and other economic impacts (such as time off work due to illness). The variant used in this study was designed to collect retrospective data on service utilization during the 12 previous months.

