The content of the modules is explained in depth later. The structure of the modules always follows the same scheme: each begins with the explanation of the contents of the module, different exercises are proposed, and then the self-test questions are presented to verify whether the explanation has been understood. If any user does not correctly answer any question, the computer program will immediately provide the correct feedback with a simple explanation. The module ends with the proposal of homework with the aim of practising what has been learned. In addition, before starting each module, a check is made to see whether the participants have carried out the proposed tasks and responds by congratulating them or encouraging them to do the task. It is very important to carry out these tasks in order to consolidate everything learned in the programme and so that the strategies offered by the programme are turned into skills. An important aspect is the possibility of reviewing the content of the different modules. The programme is designed to last 8–12 weeks. After some time without accessing the computer program (a time that can be programmed), the user will receive a reminder e-mail to continue completing the modules. The clinician can modify the period that should pass without entering to receive said reminder. The programme contents are the following:*Face-to-face session 1. Presentation of the programme:* Motivational techniques will be used to increase adherence of participants to face-to-face sessions and homework, and adherence to pharmacological treatment will be also promoted as one of the main focal points of the programme. The online computer program will be presented and patients will be trained in the procedure to log in and use it from home.*M1. Psychoeducation of depression:* The impact of depression on patients’ quality of life and functional ability, as well as on the prognosis of diabetes and other chronic diseases, will be described. The initial symptoms of depression and how to respond when they appear will be analysed. Self-control under stress will be emphasized, with patients taught to do relaxation exercises and to reward efforts and achievements made. In addition, specific techniques and very useful and practical tips to reduce stress in daily life will be explained.*M2. Healthy Life Style*: The need to carry out regular physical activity will be explained. The Mediterranean diet will be introduced, with education on the need to follow 6 healthy dietary commands. All of this will come with information and practical exercises on how to systematize food-related behaviours. Developing a social support network will be emphasized. People will be shown specific techniques on how to create and maintain an adequate social support network.*M3. Behavioural activation:* The importance of establishing and maintaining an adequate level of activity and involvement with life will be considered. Patients will be taught to schedule activities, and the need to monitor the performance of significant activities will be explained. The essential tool of this module will be the ‘Activity Diary’.*M4. Positive psychology:* This module will help patients to see the importance of positive emotions and learn procedures that generate positive experiences, encouraging involvement in pleasant and meaningful activities and contact with other people.*M5. Mindfulness and compassion*: This module will include components of Mindfulness-based Cognitive Therapy (MBCT). Core mindfulness practices will be carried out: the practice of breathing, the body scan and the 3-min exercise. The importance of establishing a regular mindfulness practice, as well as regular informal practice, will be considered. Some basic elements of compassion will be included, such as the self-compassionate pause.*Face-to-face session 2. Review of completed modules already and practice*. This is a structured session comprising: a) resolution of doubts, b) performing some of the most important practices (proposed to be done periodically at home), c) emphasizing the continuous putting into practice of the strategies learned and d) farewell and intervention closure.*M6. Relapse prevention and maintenance*: This module aims to strengthen the strategies learned during the programme. The possibility of continuing to practice the strategies learned once the treatment is completed will also be discussed, with emphasis on the fact that participants can continue to use the online computer program during the entire follow-up period (6 months) for this purpose. It will also teach participants how to identify and cope with future high-risk situations. Finally, instructions will be given to conduct follow-up evaluations.

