### Instruments

The assessor will be blind to the type of treatment that will be administered to patients. In addition, this assessor will be different from the person who collects the measurements of the study results. As far as possible, GPs will also be blind to the intervention arm to which each patient is allocated, since their intervention should be based only on usual practice, based on the criteria set out in the Guide for the Treatment of Depression in Primary Care.

Patients will be assessed at baseline (post-randomization), after the treatment, and at 3-month and 6-month follow-ups, in order to test whether the improvements achieved during the therapy are maintained in the long term. The study variables assessed are summarized in Table 2. The study flowchart is shown in Fig. 1.

**Table 2 Tab2:** Study variables

Instrument	Assessment area	Time to assessment	Applied by
PHQ-9 (40, 41)	Severity of depression	Baseline and follow-up sessions^a^	Researcher A phone Online (follow-up sessions^a^)
Glycosylated haemoglobin	Diabetes control	Baseline and follow-up sessions^a^	Online
FPS-R [42]	Pain intensity	Baseline and follow-up sessions^a^	Online
Roland-Morris Scale [43–46]	Physical limitation	Baseline and follow-up sessions^a^	Online
MINI [47]	Psychiatric diagnosis	Baseline	Researcher A phone
Sociodemographic data	Gender, age, marital status, education, occupation, economical level	Baseline	Researcher A phone
SF-12 Health Survey [48, 49]	Health-related quality of life	Baseline and follow-up sessions^a^	Online
CRSI [39, 50]	Health and social services use	Baseline and 6 months post-treatment	Researcher A phone (Baseline) Researcher B phone (6 months post-treatment)
EQ-5D-3 L [51, 52]	Quality of life related to health	Baseline and follow-up sessions^a^	Online
OFS [53]		Baseline and follow-up sessions^a^	Online

*PHQ-9* Patient Health Questionnaire, *FPS-R* Faces Pain Scale –Revised, *MINI* Mini-International Neuropsychiatric Interview, *CSRI* Client Service Receipt Inventory, *EQ-5D-3 L* EuroQol-5D-3 L, *OFS* Openness to the Future Scale

^a^Follow-up sessions: post-treatment, 3 and 6 post-treatment months

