#### Descriptions of costing procedure

Data collection on the use of health and social services will be collected through the CSRI-Spanish version [39, 50]. Costs of the study will be estimated from the healthcare and societal perspectives during the previous six months (before baseline), and during the six months of follow-up. Direct health care costs will be calculated by adding the costs derived from pharmacological consumption, use of health services and clinical tests, and costs incurred by the staff running the intervention.

The cost of medication will be calculated by determining the price per milligram during the study, according to the databases of the Spanish Ministry of Health and Consumer Affairs, including value-added tax. The total cost of medication will be calculated by multiplying the price per milligram by the daily dose in milligrams and the number of days of treatment. The main source of the unit cost data for medical tests and health services is the OBLIKUE database of health care costs [54]. The OBLIKUE database contains information about Spanish health service costs and is derived by systematic reviews of the literature. Indirect costs (lost productivity) will be calculated considering sick leave days and multiplying them by the minimum daily wage in Spain for 2018. Finally, total costs will be calculated by adding direct and indirect costs. The unit costs will be expressed in euros (€), based on 2018 prices.

The two interventions in this study will be conducted by government agencies and financed by the Carlos III Health Institute; their implementation will not incur additional costs for the Spanish National Health Service. Therefore, costs associated with the interventions in the study will not be included.

The economic evaluation of this study will follow the general guidelines for conducting pharmacoeconomic analyses in Spain. It will also follow the Guidelines of the International Society for Pharmacoeconomics and Outcomes Research (ISPOR) [55] and the Consolidated Health Economic Evaluation Reporting Standards (CHEERS) [56].

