#### Utility scores

Utility scores will be obtained from two health-related quality of life questionnaires EuroQol 5D and SF-12. QALYs will be calculated based on these scores using the Spanish EQ-5D tariffs [57]. Along with EQ-5D utility scores, scores recorded on the EQ VAS will also be used as an outcome for the analysis.

The perspective used in our analysis will be twofold: the social perspective, to include all costs and quality of life, and the perspective of the Spanish health system.

The time horizon of the study is six months, so it will not be necessary to apply a discount factor to the costs.

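### The economic evaluation's time windows contradict each other: 12-month CSRI recall, six-month costing periods and horizon, and a final visit about 7.8–8.8 months after baseline

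*Protocol article*

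**What the plan says.** All references are to the Protocol article.

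- **Recall period** (Secondary outcomes, CSRI Spanish version): the variant used is "designed to collect retrospective data on service utilization during the 12 previous months".
- **CSRI timing** (Instruments, Table 2): "Baseline and 6 months post-treatment". No other administration is listed.
- **Costing periods** (Descriptions of costing procedure): costs are estimated "during the previous six months (before baseline), and during the six months of follow-up".
- **Horizon** (Utility scores): "The time horizon of the study is six months". This is the reason given for not discounting.
- **Visits** (Instruments): "Patients will be assessed at baseline (post-randomization), after the treatment, and at 3-month and 6-month follow-ups". The Table 2 footnote sets the clock: "Follow-up sessions: post-treatment, 3 and 6 post-treatment months". EQ-5D-3L is taken at all of these visits.
- **Programme length** (Internet-delivered psychological intervention): "The programme is designed to last 8–12 weeks". The description of module 6 uses the term follow-up period for the six months after treatment ends.
- **QALYs**: Utility scores names EQ-5D and SF-12 as utility sources and adds that "QALYs will be calculated based on these scores using the Spanish EQ-5D tariffs". Cost-utility analysis specifies the area-under-the-curve technique but gives no start or end point.

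**The concern.** An incremental cost-effectiveness or cost-utility ratio has meaning only if its numerator and denominator cover the same period, and that period should begin at randomization. Here the form's recall, the costing periods, the horizon and the visit schedule describe periods of different length or with different starting points. The article does not say how they are brought together.

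Most of this an analyst could settle later, but the recall period is fixed when the data are collected. If the CSRI records totals over 12 months (an assumption, since the form is not shown), those totals cannot afterwards be split into the six-month periods that the costing section needs. The article names cost-effectiveness among its aims and counts the economic study as a strength, so the ratio should rest on a defined period.

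**Working it through.** **Inputs.** Programme 8–12 weeks; final visit 6 months after treatment; CSRI recall 12 months; stated horizon 6 months. Conversion: 1 month = 365.25 / 12 / 7 = 4.348 weeks. I assume that treatment starts at baseline, that baseline and randomization coincide, and that the post-treatment visit falls at programme end.

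**Step 1: can the six-month horizon be reproduced?**
- Counted from baseline to the last visit: 8 / 4.348 = 1.84 months and 12 / 4.348 = 2.76 months. Adding 6 gives 7.84 to 8.76 months (0.65 to 0.73 years). This does not reproduce six months.
- Counted from the end of treatment to the last visit: 6.0 months. This does reproduce it, but leaves out the treatment phase.

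**Step 2: reach of the final CSRI.** Pre-baseline reach = 12 − (baseline to last visit).
- 8 weeks: 12 − 7.84 = 4.16 months, or 4.16 / 12 = 34.7% of the recall.
- 12 weeks: 12 − 8.76 = 3.24 months, or 3.24 / 12 = 27.0% of the recall.

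The baseline CSRI already covers this stretch, so the two forms overlap.

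**Step 3: what a six-month post-treatment window omits.**
- 8 weeks: 1.84 / 7.84 = 23.5% of the time from baseline to last visit.
- 12 weeks: 2.76 / 8.76 = 31.5%.

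**Step 4: QALY span against the stated horizon, if integration starts at baseline.**
- 8 weeks: 7.84 / 6 − 1 = 30.7%.
- 12 weeks: 8.76 / 6 − 1 = 46.0%.

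**Step 5: the possible readings.**

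| Reading | Result |
|---|---|
| QALYs from baseline, costs over six post-treatment months | Different periods |
| Both over the six post-treatment months | Same period, but 1.84–2.76 months after randomization are missing from both |
| Full 12-month recall used as follow-up cost | 3.24–4.16 months of pre-baseline use included |
| Both over six months from baseline | No CSRI or EQ-5D visit at that time: the nearest visits fall at 1.84 + 3 = 4.84 to 2.76 + 3 = 5.76 months and at 7.84 to 8.76 months |

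**Step 6: illustration of how the QALY window matters.** Suppose the utility gain rises linearly to 0.05 by the end of treatment and then holds. This is my assumption and not a figure in the article. The gain over the six post-treatment months is 0.05 × 6 / 12 = 0.0250. From baseline it is (0.5 × 0.05 × 1.84 + 0.05 × 6) / 12 = 0.0288 for 8 weeks, and 0.0307 for 12 weeks with 2.76 in place of 1.84. The ratios are 1.15 and 1.23, and they do not depend on the 0.05.

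**The case against.** The strongest defence is that one coherent reading exists. If the six-month horizon and the follow-up period both mean the six months after treatment, costs and QALYs share a window and the ratio does not mix periods. Integration limits and the trimming of recall data are also details that an article may leave to an analysis plan.

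Part of this stands. A reader might infer that the ratio will include pre-randomization costs. The article does not say so: the costing section keeps the six months before baseline apart from the six months of follow-up, and pre-baseline use enters only if the 12-month recall is used untrimmed. A reader might also infer that QALYs certainly start at baseline. That is suggested by the EQ-5D schedule but stated nowhere.

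Three further limits are fair:
- The percentages above are shares of calendar time and do not measure bias in the ratio. Under individual randomization, pre-baseline use is balanced in expectation, so including it adds noise and no systematic shift.
- It is tempting to say that a six-month window drops the cost of delivering the programme. The costing section states that intervention costs are excluded (although it also lists staff running costs among direct costs, a separate inconsistency). On that exclusion, what the window loses is other service use, medication and productivity during treatment.
- The SF-12 remark concerns valuation and not time windows. An EQ-5D base case is the natural reading, so this is a minor wording point.

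What does not stand is that the coherent reading settles the matter. It leaves the treatment phase out of both costs and QALYs, and a 12-month form still does not supply a six-month period.

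**Conclusion.** The stated windows are inconsistent, and this is more than missing detail: 12-month recall conflicts with six-month costing periods, and a six-month horizon does not match a schedule that runs 7.84–8.76 months from baseline. Each reading has a defect, whether mismatched periods, an omitted treatment phase of 1.84–2.76 months, 3.24–4.16 months of pre-baseline use, or no assessment at the needed time.

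The documents support saying that costs and QALYs may cover different periods and that follow-up costs may include pre-baseline use. They do not support saying that either will happen, and no effect on the ratio can be quantified from them.

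The figures assume that treatment starts at baseline and lasts 8–12 weeks. A delay before the start would lengthen the span from baseline and shorten the pre-baseline reach. The article gives no separate end of treatment for the iTAU arm, so the span there depends on how that date is set.

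This should be fixed, but it concerns the secondary economic evaluation only. The primary clinical comparison, randomization and sample size are unaffected.

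**What to change.** 1. State one horizon for both costs and QALYs, from randomization/baseline to the 6-month post-treatment visit. Time that visit on the same clock from randomization in both arms, so that the window does not differ between arms or with each patient's programme length.
2. Set the baseline CSRI recall to the previous six months, and the final CSRI recall to the time since baseline, with the baseline date given to the interviewer.
3. In Utility scores, replace the six-month horizon with the actual length. On the article's own figures this is 7.84–8.76 months, still under one year, so not discounting remains correct.
4. In Cost-utility analysis, give the start and end points of the area under the curve, and align the follow-up costing period with them.
5. State that base-case QALYs come from EQ-5D-3L, because EQ-5D tariffs do not value SF-12 scores.

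The cost is a changed recall period on a form already in use, a scheduling rule for the final visit and a few sentences of protocol text. No extra visit is needed. The final CSRI can be changed at any time before it is first given. Baseline forms already completed with 12-month recall could be trimmed only if they record dates, so any left untrimmed should be reported as such.

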##### EuroQol-5D-3 L (EQ-5D-3 L) [51]

The utility scores were obtained from the EuroQol-5D (EQ-5D) classification system, which measures health-related quality of life on a scale of 0 (as bad as death) to 1 (perfect health). However, this two-part index may also provide negative values that correspond to health states perceived as worse than death. Part 1 records self-reported problems in each of five domains: mobility, self-care, usual activities, pain/discomfort and anxiety/depression. Part 2 records the subject’s self-assessed health on a visual analogue scale (VAS), a 10-cm vertical line along which the best and worst imaginable health states are scored between 100 and 0, respectively. The utility scores for these health states were assigned using the Spanish population rates [52].

##### Openness to the Future Scale (OFS) [53]

This 10-item instrument measures positive affectivity towards the future that can be a prospective protective factor for mental health and an indicator of psychological adjustment. The scale presents good psychometric properties in a Spanish sample.

### Ethical aspects

Informed consent will be obtained from the participants before they are aware of the group to which they are to allocated. Before they give their consent, patients will be provided with a general overview of the aims and characteristics of the study and the psychological and pharmacological intervention. Patients in the iTAU arm will be allowed to take the psychological intervention programme at the end of the study for ethical reasons. The study has been developed according to national and international standards (Helsinki and Tokyo Convention). Given that the interventions involve the use of the Internet, an important ethical issue is data protection. *Advanced Encryption Standard* (AES) strategies regarding data encryption and use of personal passwords will be implemented in order to guarantee the protection of personal information. The data will be treated anonymously and will only be used for the purposes of the study. The confidentiality of the participants included in the study will be guaranteed. Finally, the study protocol was approved by the Research Ethics Committee of each autonomous community: (CEICA in Aragon, CEIC in the Balearic Islands and the Regional Ethics and Research Committee of the province of Malaga, Andalusia).

